## Abstract

**Introduction:**

Food cravings are common in pregnancy and along with emotional eating and eating in the absence of hunger, they are associated with excessive weight gain and adverse effects on metabolic health including gestational diabetes mellitus (GDM). Women with GDM also show poorer mental health, which further can contribute to dysregulated eating behaviour. Food cravings can lead to greater activity in brain centres known to be involved in food ‘wanting’ and reward valuation as well as emotional eating. They are also related to gestational weight gain. Thus, there is a great need to link implicit brain responses to food with explicit measures of food intake behaviour, especially in the perinatal period. The aim of this study is to investigate the spatiotemporal brain dynamics to visual presentations of food in women during pregnancy and in the post partum, and link these brain responses to the eating behaviour and metabolic health outcomes in women with and without GDM.

**Methods and analysis:**

This prospective observational study will include 20 women with and 20 without GDM, that have valid data for the primary outcomes. Data will be assessed at 24–36 weeks gestational age and at 6 months post partum. The primary outcomes are brain responses to food pictures of varying carbohydrate and fat content during pregnancy and in the post partum using electroencephalography. Secondary outcomes including depressive symptoms, current mood and eating behaviours will be assessed with questionnaires, objective eating behaviours will be measured using Auracle and stress will be measured with heart rate and heart rate variability (Actiheart). Other secondary outcome measures include body composition and glycaemic control parameters.

**Ethics and dissemination:**

The Human Research Ethics Committee of the Canton de Vaud approved the study protocol (2021-01976). Study results will be presented at public and scientific conferences and in peer-reviewed journals.

STRENGTHS AND LIMITATIONS OF THIS STUDYThis prospective observational study fills the knowledge gap regarding brain responses to food viewing during and after pregnancy.This study includes subjective (questionnaires) and objective methodologies (electroencephalography (EEG), Auracle device, Actiheart) to investigate brain responses to food viewing, eating behaviours and stress responses during and after pregnancy.The study will link the outcomes of physiological and behavioural measures.We will compare eating behaviours between healthy women and women with gestational diabetes, both cross-sectionally and prospectively.Limitations include a small sample size (but comparable to other EEG studies with a similar design) and fact that all analyses (and the correlation of their outcomes) are exploratory, given the lack of data in pregnancy or the post partum.

## Introduction

### Metabolic health and eating behaviours

The prevalence of obesity continues to increase worldwide.^1^ In the USA, 35.7% of women of reproductive age (20–39 years) are obese^2^ and this prevalence exceeds 20% in high-income western countries in general.^3^

The widespread and unrestricted access and intake of foods high in sugar and fat contribute to the obesity epidemic. Foods high in sugar (carbohydrates) and fats, such as chocolate, sweet desserts and salty snacks are the most frequently craved foods.^4^ Sugar strongly stimulates the reward system, which can trigger compulsive eating.^5^ Eating behaviour refers to a variety of eating practices. This includes cognitive restraint, disinhibition with high responsiveness to external food cues and susceptibility to hunger.^6^ Disinhibited eating behaviour reflects a tendency to overeat. This can happen in the context of negative emotions (such as anxiety, depression, anger and loneliness) and/or in response to a high food palatability.^7^ Disinhibited eating behaviours can be associated with compulsive intakes of high energy-dense foods rich in fat and sugar, which contribute to obesity and poorer long-term metabolic health.^7^ The ideal situation whereby eating behaviours are regulated by appetite and food consumption is challenged by disinhibited eating behaviours.^8^

Another aspect of eating behaviour that relates to metabolic health is eating rate. Studies showed that faster eating rate is associated with increased food intake^9^ and an increased risk of obesity.^10^ A meta-analysis of the cross-sectional and longitudinal association between eating speed and metabolic outcomes showed that faster eating rate is associated with higher risks for the metabolic syndrome, central obesity, elevated blood pressure and increased fasting plasma glucose compared with slower eating.^11^

### Brain regions in relationship to food cues

Although the underlying cause(s) of food cravings are not deeply understood, it has been shown in the general, non-pregnant population that cue-induced cravings in response to food pictures predict disordered eating and excess weight gain. In a meta-analytical review of 45 studies, exposure to food stimuli (pictures) and the experience of craving influence eating behaviour and further weight gain independently of baseline body mass index (BMI), age and gender.^12^

Some people are more susceptible to an obesogenic environment. This can be also mediated through different brain responses to food in key areas. The few existing clinical data show that reward-related brain regions may be involved in excess weight gain.^13^ ‘The reward circuit is a complex neural network’ (the cortico-ventral basal ganglia circuit), which consists, among other, of the orbitofrontal cortex, anterior cingulate cortex and the ventral striatum which is part of the basal ganglia.^14^ The ventral striatum receives information from the orbital prefrontal cortex, the insular cortex, the cingulate cortex and also the amygdala, which is also closely linked to sensory processing.^14^ These reward-related brain regions are stimulated when viewing the craved foods and through unconscious processes of learning/conditioning mechanisms, promote further greater ‘wanting’ and seeking of these foods.^15^ This could be related to the fact that higher intake of foods rich in fat and sugar can reduce reward thresholds in the limbic striatal pathways and the amygdala.^15–17^ This then promotes further food craving, further increases the neural reactivity to food cues in reward-related brain regions even more, and can thus promoting a higher intake of palatable foods whether in a hungry or satiated state.^15 16 18^ Investigating the brain’s response to food with different fat and carbohydrate content may help to understand these mechanisms and their relationship to eating behaviour and metabolic health. So far, this has been mostly studied in healthy subjects.

Furthermore, physiological and metabolic parameters are also related to how the brain reacts to the sight of food. Response to viewing high-energy and low-energy foods differ between obese and healthy weight subjects.^19^ In an functional MRI (fMRI) study, overweight and obese participants demonstrated greater activation in reward-related brain regions, like the ventral striatum and anterior cingulate compared with normal weight subjects.^19^ Insulin resistance and type 2 diabetes mellitus (DM2) are associated with changes in brain responses to food stimuli.^20^ In patients with DM2, cross-sectional studies using fMRI revealed that compared with controls, responses to viewing food pictures are stronger in the ventral striatum and cortical regions, such as the insula and the orbitofrontal cortex, which are related to reward-related circuits, in comparison to controls.^20^

### Stress, emotions and eating behaviour

Emotions and stress can influence food choices and eating behaviour.^21 22^ Studies showed that there is a link between negative mood, stress and the intake of high-fat, high-carbohydrate-hyperpalatabable food and higher overall food intake, which contribute to an increased risk for obesity.^22 23^ Food cravings and overeating in response to stress and negative mood are particularly relevant in people who engage in more frequent emotional eating.^23–25^ In an fMRI study, people who engage in more frequent emotional eating had stronger responses to high-calorie food in reward-associated areas (anterior cingulate cortex) when being in a negative mood in comparison to people who do not engage in more frequent emotional eating.^26^

These results together demonstrate that there is a link between brain responses to food viewing and metabolic health, but also stress and emotions and that reward-related brain regions play a role in the regulation of food intake.

### Pregnancy

Maintaining a healthy body weight is particularly important during pregnancy, as it impacts on the health of the mother and her offspring.^27^ Maternal obesity and overnutrition during pregnancy affect the infant’s metabolic programming and increase its risk of obesity, type 2 diabetes and cardiovascular disease in the future.^28^

Nevertheless, around 28% of women gain more weight than recommended^29^ and excessive gestational weight gain (GWG) is associated with adverse perinatal outcomes such as pre-eclampsia, hypertension in pregnancy, gestational diabetes, preterm birth, caesarean section and small or large size for gestational age at birth.^30^ Higher GWG is also associated with greater postpartum weight retention (PPWR) and increasing the risk for future diabetes.^31^

During pregnancy, there is a change in eating behaviour that can have long-term effects for the mother’s metabolic health.^32^ Food cravings are frequent and concern around 40% of pregnant women.^33^ They typically begin at the end of the first trimester, peak in their frequency and intensity in the second and third trimester, and decrease after delivery.^34^ Higher food cravings during pregnancy have been associated with higher mean energy intake and GWG.^33^

Emotions and stress also influence eating behaviour in pregnancy.^35^ Emotional cues such as negative affect can trigger the craving for high-fat foods in pregnant women which is associated with excessive GWG.^8^ Similarly, under stress, pregnant women are more likely to increase cravings for pleasurable food.^36^ There are no data regarding brain responses to food during pregnancy (using either MRI or electroencephalography (EEG)) or regarding the impact of emotions or stress on these brain responses.

Regarding metabolic health, insulin resistance increases in pregnancy and around 16% of pregnant women worldwide develop gestational diabetes mellitus (GDM).^37^ GDM is defined as glucose intolerance with the first onset during pregnancy without fulfilling the criteria of overt diabetes.^38^ Women with GDM are at higher metabolic risk, have more perinatal complications such as pre-eclampsia or caesarean section^39^ and also have a higher prevalence of mental health problems in pregnancy such as depression.^40^

### Postpartum period

There is a lack of data regarding eating behaviours in the post partum and its relationship to PPWR.^32^ Existing studies showed that higher restrained and also higher intuitive eating are associated with postpartum weight loss.^32^ Knowledge related to cravings and emotional eating in the post partum is limited. Negative emotions play a role in eating behaviour during this period, leading to increased food intake and contributing to PPWR.^41^ Regarding the group of women of higher metabolic risk, those with GDM have more adverse maternal health outcomes in the post partum such as higher PPWR, a 7–10 fold higher risk of diabetes^42^ and an increased risk for cardiovascular disease.^43 44^ GDM is also associated with higher risk of post partum depression^45^ which is also associated with a less healthy diet.^46^

### Electroencephalography

EEG and visual evoked potentials (VEPs; patterns of electrical activity in the brain in response to a visual stimulus) to food viewing offer the advantage of disentangling the temporal as well as spatial dynamics of perception, while fMRI only unravels spatial aspects, that is, brain regions. Some VEP studies have shown differential responses to pictures of high and low-energy foods.^47^ Reward-related and (inhibitory) control-related processes are partially recruiting the same neural sources, yet with varying temporal dynamics.^48^ Existing studies on food cravings during and after pregnancy only assessed different kinds of food cravings and their frequency with questionnaires and did not involve brain responses to food cues. Results from these studies have been inconsistent. We are not aware of any human studies investigating objective correlates or mechanistic pathways of cravings in pregnancy. In order to better understand food cravings and metabolic health outcomes in pregnancy and post partum, investigating the neural activities of the brain pathways in response to cravings induced by food viewing during and after pregnancy might lead to novel clinical treatment options.

Overall, the relationship between weight, GWG, PPWR and adverse perinatal and metabolic health outcomes in the perinatal period and the difficulty to reduce weight or weight gain, highlight the need for novel approaches to understand eating behaviour and metabolic health during pregnancy and the post partum, especially in metabolic high-risk women with GDM.

As there are no data regarding brain responses to food in pregnancy and in the post partum, we designed an observational prospective study whose design is exploratory. Nevertheless, based on the above-mentioned data, we hypothesised that brain responses, especially to food high in fat and carbohydrate content would differ between pregnancy and the post partum and between healthy women and women at higher metabolic risk such as GDM. We also hypothesised that there would be a relationship between brain responses to viewing food with different fat and carbohydrate content, eating behaviour and metabolic health and that negative emotions and higher stress levels might influence these brain responses as well as eating behaviour in the perinatal period.

### Aims of the present study

The overall aim of this observational study is to investigate brain responses to viewing pictures of foods of different fat and carbohydrate contents in women during pregnancy and in the post partum and their relationship with eating behaviour and metabolic health. We will investigate this in healthy women and in a metabolic high-risk group, that is, women with GDM to include a wide spectrum of metabolic health.

The main objectives are as follows:

Objective 1: To investigate differences in brain responses to food pictures of varying fat and carbohydrate content (HIGH-FAT/LOW-CARB; HIGH-FAT/HIGH-CARB; LOW-FAT/LOW-CARB; LOW-FAT/HIGH-CARB) during and after pregnancy, in women with and without GDM.

Objective 2: To investigate the cross-sectional and longitudinal relationships between brain responses to food viewing with reported food cravings, eating behaviour and metabolic health outcomes such as weight, body fat and glucose control during pregnancy and in the post partum.

Objective 3: To investigate differences in brain responses to food pictures in relationship to different emotional states and stress levels.

## Methods

### Study design

This is a prospective observational study of women with and without GDM. There will be two visits (at 24–36 weeks gestational age and 6 months post partum). Both visits will take place at Lausanne University Hospital.

### Study population, inclusion and exclusion criteria, and recruitment

We will include 40 women with valid data for the primary outcomes (20 women with GDM and 20 healthy controls) at both time points. In the initial tests, the EEG data of 14 women with GDM and 13 healthy controls were not valid (ie, too much noise, low quality of signal), which has been corrected since. We will therefore recruit at least 35 women with GDM and at least 34 healthy controls, in their 24–36 weeks of pregnancy, during their antenatal appointments visits at a Swiss University Hospital. GDM women (clinical group) will be recruited at the GDM clinic whereas healthy pregnant women without GDM (control group) will be recruited at the hospital’s ambulatory clinic.

For women with GDM, inclusion criteria are: gestational age 24–36 weeks, age ≥18 years, GDM diagnosed at 24–32 gestational weeks according to IADPSG and ADA criteria.^49 50^ For healthy controls, inclusion criteria include women with normal weight (prepregnancy BMI <25 kg/m2), with no prior or current GDM, no diets and weight changes above 5 kg in the last 5 years (except for pregnancy), no excessive pregnancy weight changes (less than twice of the Institute of Medicine recommendations).^51^ Women in both groups should be able to fluently speak and write either French or English.

Exclusion criteria include: pre-existing diabetes, eating disorders (Anorexia Nervosa, Bulimia Nervosa and Binge-Eating Disorder), vegetarian/vegan diet, uncontrollable nausea and vomiting, current insulin treatment, participation in an intervention study, current medication to treat psychiatric disorders, active suicidal thoughts.

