### Data management and statistical analyses

#### Statistical analysis plan

The sample size is based on previous EEG studies of similar design,^23 25^ but all analyses are exploratory, as to our knowledge so far no such study has been conducted during pregnancy or the post partum period. Statistical analyses will be performed with STATA V.15.1 (2017) and MATLAB V.9.5 (R2018b). Processing of the EEG data will be performed using Cartool software and statistical software.^52^ Demographic and other descriptive variables will be represented as means and SD or percentages where appropriate. Analysis of variance, t-tests or χ^2^ tests will be used to determine group differences between responses to food and non-food pictures, different food categories, brain responses between pregnancy and post partum states, between women with and without GDM and between normal weight and overweight/obese women. Regression analyses will be used to model the relationships between predictor variables and outcomes (such as between brain responses to food viewing with intuitive eating and metabolic health such as weight, body fat and glucose control). In the second step, we will investigate the impact of covariates, where appropriate, such as maternal age, gestational age and prepregnancy BMI on outcomes and adjust for them if necessary.

Twenty women with valid data for the primary endpoint in each group (n=40) will be investigated during pregnancy and at 6 months postpartum. In order to achieve this, we had to include more patients.

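### Only controls are capped at prepregnancy BMI below 25, so the pooled weight-status comparison is confounded with GDM and the unadjusted GDM contrast is confounded with BMI and weight history

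*Protocol article*

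**What the plan says.** The protocol article, under Study population, inclusion and exclusion criteria, and recruitment, sets different entry rules for the two groups.

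- Controls: "inclusion criteria include women with normal weight (prepregnancy BMI <25 kg/m2), with no prior or current GDM". They must also have "no diets and weight changes above 5 kg in the last 5 years (except for pregnancy") and "no excessive pregnancy weight changes (less than twice of the Institute of Medicine recommendations").
- GDM group: "For women with GDM, inclusion criteria are: gestational age 24–36 weeks, age ≥18 years, GDM diagnosed at 24–32 gestational weeks". The list contains no limit on BMI, dieting or weight change, and neither do the exclusion criteria common to both groups.

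The analysed sample is 20 women per group. The Primary outcome section compares visual evoked potentials between women with and without GDM. The Statistical analysis plan section lists group comparisons "between women with and without GDM and between normal weight and overweight/obese women" and does not confine the weight-status comparison to one group. Prepregnancy BMI appears there as an example of a covariate to be examined in a second step and adjusted for only if that proves needed. Dieting and weight history are not among the covariates named. The Introduction, under Brain regions in relationship to food cues, states: "Response to viewing high-energy and low-energy foods differ between obese and healthy weight subjects".

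**The concern.** The entry rules leave one cell of the design empty: no control can have a prepregnancy BMI of 25 or more. Two of the planned between-group comparisons therefore overlap. A pooled weight-status test sets a group made up only of GDM women against a group that contains all the controls. An unadjusted GDM test sets women of any BMI and weight history against women selected to be lean and weight-stable. The article's own background gives reason to expect that weight status is related to the response to food pictures. A difference found in either test could then be credited to the wrong factor.

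The entry rules also touch secondary outcomes. Weight, body composition and cognitive restriction are compared between groups of which only one was screened on weight and dieting, so part of any difference there comes from selection.

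**Working it through.** **The plan's own figures.** The document gives no figure for the overlap of GDM and BMI, and no alpha, power, effect size or SD behind the 20 per group, so there is no power calculation to reproduce. The recruitment targets can be followed: 20 + 14 = 34 for GDM and 20 + 13 = 33 for controls, against stated targets of at least 35 and at least 34. That agrees to within one woman and has no bearing on this point.

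**Inputs.** From the document: 20 GDM women, 20 controls, no control with prepregnancy BMI of 25 or more. Assumed: the share *f* of GDM women with BMI of 25 or more, varied from 0.2 to 0.8; a true effect of 0.8 SD; SD 1; two-sided alpha 0.05; normal approximation.

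**Cells.** Overweight/obese: 20*f* GDM women, 0 controls. Normal weight: 20(1 − *f*) GDM women, 20 controls. Because one cell is empty, an interaction of GDM with BMI category cannot be estimated at any *f*.

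**Spurious GDM contrast** (only BMI category has an effect, 0.8 SD). The groups differ in the share overweight by *f* − 0, so the expected difference is 0.8*f*, with standard error √(1/20 + 1/20) = 0.316. At *f* = 0.5 this is 0.40 SD.

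**Spurious weight-status contrast** (only GDM has an effect, 0.8 SD). The share with GDM is 1 among overweight women and 20(1 − *f*)/[20(1 − *f*) + 20] among normal-weight women. The expected difference is 0.8 × 20/[20(1 − *f*) + 20]. At *f* = 0.5 this is 0.8 × 20/30 = 0.53 SD, with standard error √(1/10 + 1/30) = 0.365.

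| Share *f* | Overweight GDM / normal-weight GDM | Spurious GDM contrast (rejection rate) | Spurious weight-status contrast (rejection rate) | Correlation of the two indicators | Variance inflation |
|---|---|---|---|---|---|
| 0.2 | 4 / 16 | 0.16 SD (8%) | 0.44 SD (13%) | 0.33 | 1.13 |
| 0.5 | 10 / 10 | 0.40 SD (24%) | 0.53 SD (31%) | 0.58 | 1.50 |
| 0.8 | 16 / 4 | 0.64 SD (53%) | 0.67 SD (54%) | 0.82 | 3.00 |

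The nominal rejection rate is 5%.

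**Does BMI adjustment help?** Simulation with 20 per group, GDM BMI normal with mean 26 to 30 and SD 5 (above 18), control BMI normal with mean 22.5 and SD 2.5 cut at 25, a linear slope of 0.1 SD per BMI unit, and no GDM effect (all assumptions). The unadjusted GDM difference is 0.46 to 0.81 SD. With BMI as a linear covariate it is about 0.01 SD or less in absolute value, with rejection at about 5%. Adjustment therefore works when the assumed form is right. Above BMI 25 there are no controls against which to check that form.

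**Cost of restricting to BMI below 25.** Only normal-weight GDM women then inform the GDM contrast. Power for 0.8 SD is 0.72 with 20 versus 20, and falls to 0.66, 0.54 and 0.31 with 16, 10 and 4 GDM women (*f* = 0.2, 0.5, 0.8).

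**The case against.** The strongest case for the plan has four parts.

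- **The contrast is deliberate.** The Aims section sets healthy women against a metabolic high-risk group so as to span a wide range of metabolic health, nowhere claims a GDM effect independent of BMI, and all analyses are declared exploratory. This stands as a defence of recruiting lean controls. It does not justify listing GDM and weight status as two separate tests when the design ties them together, and the stated limitations do not mention the overlap.
- **BMI is already named as a covariate.** A reader might infer that adjustment cannot rescue the GDM contrast. The documents do not support that: with a linear relation common to both groups, adjustment removes the bias and costs only precision. What remains is that adjustment is conditional, rests above BMI 25 on an unchecked form, and does not by its stated examples cover dieting and weight history.
- **The weight-status test is not fully specified.** Neither its population nor the BMI it uses is stated, and a control could exceed 25 at six months post partum. This stands as a qualification: the empty cell is certain only for prepregnancy BMI, and the confounding applies if the test is pooled, as the sentence reads.
- **The background evidence is indirect.** It is an association from functional MRI, not a finding about evoked potentials in pregnancy. So BMI is a plausible confounder here, not a demonstrated one.

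**Conclusion.** The concern holds for two between-group comparisons. By prepregnancy BMI, a pooled weight-status comparison is confounded with GDM, and the unadjusted GDM contrast is confounded with BMI and weight history. Both follow from the entry criteria without any outside figure. The size does not: it depends on the unknown BMI distribution of the GDM women and on an assumed effect of 0.8 SD, which together give the ranges tabulated above. If no GDM woman had a BMI of 25 or more, the confounding with BMI category would vanish, but the planned overweight/obese group would be empty.

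A reader might go further and infer that Objective 1 cannot be answered. The documents do not support this. That objective also covers food category and pregnancy versus post partum, which are comparisons within women and are not affected as main effects. Nor can one say that any GDM finding would be wholly a BMI effect; at the lower assumed shares the spurious part is small.

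**What to change.** 1. State that the comparison of normal-weight with overweight/obese women is made within the GDM group only, and name the BMI used to classify them. This leaves at most 20 women, for example 10 versus 10 at *f* = 0.5.
2. Make adjustment of the GDM contrast for prepregnancy BMI fixed in advance. Note beside it that above BMI 25 the estimate relies on the assumed form of the BMI-response relation, because there are no controls there. Add a sensitivity contrast of GDM versus control in women with BMI below 25.
3. Describe the full-sample contrast as GDM with unrestricted BMI versus lean healthy controls, and state that group differences in weight and cognitive restraint are partly set by the entry criteria.

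These are changes of analysis and wording. They need no new data and no change to control eligibility. The cost is precision, as in the power figures above, and the sensitivity contrast speaks only to GDM in normal-weight women.
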